### Randomization and blinding

The randomization (in blocks of 15) list was computer-generated by an independent statistician not involved in participant management. The resulting sequence (randomization number and treatment arm) is stored in opaque sealed envelopes. The enrolling clinician assigns a study number to the participant. The study nurse implements the treatment allocation by opening a sealed envelope for each child according to the assigned randomization number. The laboratory staff are blinded to the treatment allocation, but participants, clinical staff, and data analysts are not.

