### Criteria for withdrawal or discontinuation from the study

The objective criteria for discontinuation from study medication and/or institution of another form of treatment include the following:Parent/guardian’s withdrawal of consentDevelopment of a concomitant illness that would interfere with the clear interpretation of study outcomesInability to retain study medication due to vomitingAny serious adverse event requiring treatment withdrawal in the opinion of the study clinician or at the request of a parent/guardianMajor protocol violation, omission of more than one treatment dose, or a credible report of self-medication with an additional anti-schistosomal or antimalarial drug outside the study protocol

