### Adverse events

The study nurse administers all the study drugs. Children will ingest the study drugs with a small amount of water. Before administering the study treatment, all the children are given a light meal (slices of bread and a glass of orange juice) to reduce the study drugs’ nauseating effect and improve drug bioavailability [32]. Participants are observed for 1 h after drug ingestion to ensure retention and to assess for any immediate adverse events. Participants who vomit within 1 h of drug ingestion are re-dosed. Participants with repeated vomiting are withdrawn from the study.

All adverse events are elicited by asking the children about any adverse drug reactions observed after taking the study drugs. The symptoms will be assessed, graded (according to their intensity as perceived by the child) by the study clinician, and recorded on the adverse event form. The adverse events form is administered an hour after study treatment and 24 h later (before the next ACT dose). The following information is recorded on the adverse events form: adverse event description, duration (start and end dates); severity grade (mild, moderate, severe); causality (relationship to the study drugs); action(s) taken; and the outcome. The participants who develop adverse events (AEs) or serious adverse events (SAEs) are treated appropriately and followed up until they return to a normal state of health. The investigator reports any SAE occurring or observed during the follow-up period to the KEMRI Scientific and Ethics Review Unit within 48 h of being aware of the event.

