### Data management and analysis

Data collected from each participant is recorded on paper-based case report forms (CRFs) in black ballpoint pen. The principal investigator will ensure that the data in the CRFs are accurate, complete, and legible. Data from the case record forms is entered by a data clerk into computers as they accrue using the MS Access program. The data is verified by comparing it with the CRFs. Missing data is imputed as either treatment success or treatment failure (assuming the same infection intensities before and after treatment). Validated data is transferred to SPSS version 20 and STATA version 12 for statistical analyses. The CRFs and the electronic data will be kept for 5 years after the primary manuscripts are published.

Data is analyzed using SPSS for Windows version 20 (SPSS Inc., Chicago, IL) and STATA version 12.0 (StataCorp., College Station, TX, USA) packages. A two-sided *p*-value less than 0.05 is considered statistically significant for all tests.

Demographic and other baseline characteristics are compared to check for imbalances between the study groups. These measures will be tabulated from the intent-to-treat population. Significance tests are not performed to compare the differences between study groups at baseline. Where imbalances are suspected, additional analyses are performed to adjust for these variables.

To determine efficacy, both the per-protocol and intention-to-treat analyses are done, but the per-protocol analysis is the main approach. The primary efficacy outcome is the cure rate, defined as the proportion of children infected with *S. mansoni* at enrollment but not excreting eggs by week 6 after taking the study treatment. In the computation of the cure rate, children randomized to the PZQ alone study arm are considered the control group. Cure rates are compared between the treatment groups using Pearson’s chi-square test for contingency tables (in a per-protocol analysis) and summarized as absolute risk differences with 95% confidence intervals (CI). The per-protocol population is defined to include all participants who were randomized and who completed the study procedures to week 6 or 12. The primary hypothesis for non-inferiority is assessed by considering the lower limit of the 95% CI for the risk difference. Non-inferiority is concluded if the lower bound of the 95%CI from the risk difference does not exceed the non-inferiority margin of − 10.

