The cumulative cure rate at week 12 is assessed by calculating a two-sided difference in proportions of cured children from each PZQ plus ACT arm compared with the PZQ alone arm. Arithmetic mean (AM) egg counts are computed for all non-cured participants. The egg reduction rate is computed as (1 − (AM EPG after treatment/AM EPG before treatment)) × 100. The ERR is expressed as a percentage. Re-infection rate is the proportion of children who test negative for *S. mansoni* at week 6 but test positive at week 12 follow-up. Changes in continuous variables over time are assessed using analysis of variance (ANOVA). The least significant difference will be used to assess post hoc pair-wise comparisons between the group means. Logistic regression will be used for analyses adjusted for the treatment received.

For the primary safety analysis, the frequency and pattern of adverse events are computed by patient counts and percentages in each of the five treatment groups. Adverse events are computed for all participants who received at least one dose of the study drug (intention-to-treat population).

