#### Withdrawal

Participation is voluntary, and participants can withdraw from the study at any time and for any reason without consequences. Participants will be withdrawn from the study due to repeated vomiting or occurrence of SAE. Children with SAEs are followed up until the end of 6 weeks after the last treatment dose. Participants withdrawn from the study due to medical reasons are referred to adequate health facilities for further care. Unless consent is withdrawn, efforts are made to assess these children at the week 6 follow-up schedule.

Valid reasons for study discontinuation include completion of the scheduled follow-up period and exclusion from follow-up. Randomized participants who miss one or more scheduled follow-up visits remain in the study and are followed up as planned. Loss to follow-up is expected to be minimal because all the participant-related study procedures are completed at school and, if necessary, at home. In the unlikely event that a study participant moves away from the study area during the study period, they are considered lost to follow-up and are not included in the efficacy analysis. However, data collected up to the time of withdrawal will remain in the study and be used for analysis of whether or not the participant continues with the follow-up visits. Participants who have been withdrawn from the study are administered a standard dose of praziquantel after the final study visit. No additional participants are recruited to replace those who have withdrawn.

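### The main per-protocol set names no adherence criterion and does not require a week-6 stool, and the missing-data rules are open enough to reverse the non-inferiority conclusion if loss differs between arms

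*Protocol article*

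**What the plan says.** All references are to the protocol article.

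- **Main set.** Data management and analysis plans both a per-protocol and an ITT efficacy analysis, "but the per-protocol analysis is the main approach". The set is defined in one sentence: "The per-protocol population is defined to include all participants who were randomized and who completed the study procedures to week 6 or 12".
- **Deviations.** Criteria for withdrawal or discontinuation from the study lists major protocol violation, "omission of more than one treatment dose, or a credible report of self-medication with an additional anti-schistosomal or antimalarial drug". The per-protocol definition does not refer to this list.
- **Missing data.** Data management and analysis states: "Missing data is imputed as either treatment success or treatment failure". A bracket adds that infection intensity is taken to be the same before and after treatment.
- **Children who move away.** Withdrawal says that "they are considered lost to follow-up and are not included in the efficacy analysis". The same section keeps children who miss visits in the study, tries to assess medically withdrawn children at week 6, and uses data collected up to withdrawal.
- **ITT.** The only definition given is in the safety paragraph: "all participants who received at least one dose of the study drug (intention-to-treat population".
- **Blinding.** Laboratory staff are blinded, but "participants, clinical staff, and data analysts are not".

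The primary efficacy endpoint (Outcomes) is cure at week 6. Non-inferiority is judged on the lower 95% limit of the risk difference against -10 points.

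**The concern.** A per-protocol set is meant to show the treatments as actually taken. As worded, this one is a completer set. A child who missed more than one dose or took another anti-schistosomal drug can qualify if follow-up was completed. Keeping such children tends, though not always, to make arms look alike, and in a non-inferiority comparison that favours the claim. The phrase covering week 6 or week 12 also leaves open whether a child seen only at week 12 belongs in the week-6 analysis.

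The missing-data sentence permits two opposite codings, and its bracket fits only one of them: unchanged intensity in an infected child is failure. The Withdrawal section adds a third handling, exclusion, for children who move away. An ITT efficacy analysis cannot include everyone randomised and also leave these children out.

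Loss could differ between arms by design. The combination arms are dosed on three days and the control on one, and "Participants with repeated vomiting are withdrawn from the study". If it does differ, the choice among the three handlings affects the primary result, and the analysts know the allocation.

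**Working it through.** **Inputs from the document (Sample size; Data management and analysis).** 102 per arm before loss, 5% loss, 108 randomised per arm, 72% cure on praziquantel, margin 10 points, decision on the lower 95% limit. The loss step reproduces: 102/0.95 = 107.4, rounded up to 108, and 5 × 108 = 540. How the 102 arose is a separate question and is not used here.

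**Assumptions.** The numbers missing and the cure counts are illustrative. The interval is Wald, since the article names no method.

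**Formula.** With combination arm 1 and praziquantel arm 0, d = p1 − p0, SE = √[p1(1−p1)/n1 + p0(1−p0)/n0], lower limit L = d − 1.96 × SE.

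**Room for results near the margin.** At 72% in both arms and 102 each, the half-width is 1.96 × √(2 × 0.72 × 0.28/102) = 12.3 points, so a lower limit near -10 is quite possible.

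**Equal loss, 6 per arm (about 5%); cured 73/102 praziquantel, 75/102 combination.**

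| Handling | Combination | Praziquantel | d | L | Above -10? |
|---|---|---|---|---|---|
| Completers | 75/102 | 73/102 | 1.96 | -10.28 | No |
| Missing = success | 81/108 | 79/108 | 1.85 | -9.83 | Yes |
| Missing = failure | 75/108 | 73/108 | 1.85 | -10.53 | No |

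The spread is 10.53 − 9.83 = 0.70 points. The verdict changes only because the counts sit at the margin. With 79/102 in the combination arm the three limits are -6.05, -5.82 and -6.60, and all pass.

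**Unequal loss, 3 praziquantel and 9 combination (12/216 = 5.6% overall); cured 76/105 and 76/99.**

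| Handling | Combination | Praziquantel | d | SE | L | Above -10? |
|---|---|---|---|---|---|---|
| Completers | 76/99 = 76.8% | 76/105 = 72.4% | 4.39 | 6.09 | -7.54 | Yes |
| Missing = success | 85/108 = 78.7% | 79/108 = 73.1% | 5.56 | 5.81 | -5.82 | Yes |
| Missing = failure | 76/108 = 70.4% | 76/108 = 70.4% | 0.00 | 6.21 | -12.18 | No |

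The two imputation directions differ by 12.18 − 5.82 = 6.36 points, and the conclusion reverses.

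**The passages side by side.** The missing-data sentence gives every missing outcome a value but names no set. The per-protocol definition drops children who did not complete procedures. The Withdrawal section drops children who move away from the efficacy analysis as a whole. No sentence assigns these rules to different analyses.

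**The case against.** The strongest reply is that a coherent reading exists: exclude in per-protocol, impute in ITT, and treat success and failure as best and worst bounds. That is possible, but the article does not say it, and the unrestricted exclusion in Withdrawal cuts across it.

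Other points on that side carry weight:

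- **Dosing may be implied.** Table 1 lists dosing among the scheduled procedures, so completing procedures may be meant to include it. Dosing is also directly observed. The gap is an unstated criterion, not a decision to keep non-adherent children.
- **Loss may be small.** Home visits are planned and minimal loss is expected. With equal loss the rule barely matters.
- **The ITT label is minor.** Table 1 puts randomisation and the first dose on the same day, so the at-least-one-dose set should nearly equal all randomised.
- **Much detail belongs in an SAP,** which is not shown. The rules at issue here, however, are ones the article itself states.

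A reader might infer more than the text supports. One inference is that every child without a week-6 stool is both excluded and imputed. The explicit exclusion covers only children who move away; children who miss visits stay in the study. Another is that children withdrawn for vomiting or a serious adverse event are necessarily dropped, whereas week-6 assessment is attempted for those withdrawn for medical reasons. A third is that heavier imbalance proves reversal. With 12 combination and 2 praziquantel children missing and completer cure of 70% against 72%, the difference runs from -8.4 to +0.8, but the lower limits are -14.5 (completers), -21.0 (failure) and -11.0 (success). All fail, so that case shows a large shift and no reversal.

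**Conclusion.** The point holds as a defect in stated rules. The main set names no adherence criterion and does not require the week-6 stool, the imputation sentence fixes neither direction nor set, and the move-away exclusion conflicts with the planned ITT analysis. The effect is under 1 point on the lower limit with equal loss near 5% and one common rule. It is about 6 points, enough to reverse the conclusion, with an assumed 3 against 9 missing. The size rests on assumed counts and a Wald interval; nothing in the document shows that loss will be unequal. Nor does it show that anyone intends to choose a rule after seeing results. Unblinded analysts make it more important to close the choice in advance but are not evidence of misuse.

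**What to change.** Settle the following before analysis:

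1. Define the week-6 per-protocol set as randomised children with an evaluable week-6 stool and none of the deviations already listed under Criteria for withdrawal or discontinuation. Define a separate week-12 set.
2. Define the efficacy ITT set as all randomised children, analysed as randomised. Count a missing week-6 stool as failure in every arm as the single primary rule, and use missing as success only as a sensitivity bound.
3. Limit the exclusion of children who move away to the per-protocol set.
4. Call the at-least-one-dose set the safety set.
5. Conclude non-inferiority only if the per-protocol and ITT lower limits are both above -10.
6. Fix set membership by prespecified rules, without sight of the week-6 results. Masking arm codes alone would not blind this step, because dosing records show one day or three.

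The cost is mainly wording, plus a slightly lower chance of claiming non-inferiority. Deviation-based exclusion may fall more on the three-day arms, which is a reason to require ITT as well. Trial status gives follow-up to September 2023; if analysis has already begun, the report should say when the rules were fixed and show the result under each handling.

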**Methods:**

The SCHISTOACT study is an open-label, head-to-head, five-arm, proof-of-concept, non-inferiority, individually randomized controlled trial with a follow-up of 12 weeks. A total of 540 primary school-aged children from the Mwea area, Kirinyaga County in central Kenya, diagnosed with *S. mansoni* infection (by Kato-Katz method) are randomly allocated (1:1:1:1:1) to a single dose of praziquantel plus a 3-day course of artesunate-sulfalene/pyrimethamine, or artesunate-amodiaquine, or artesunate plus mefloquine, or dihydroartemisinin-piperaquine, or praziquantel control arm. The primary endpoints are efficacy (cure rate, assessed by microscopy) and safety (adverse events) of each study arm 6 weeks after treatment. Secondary endpoints include cumulative cure rate, egg reduction rate, and re-infection 12 weeks after treatment. The non-inferiority margin is set at − 10 for the risk difference in cure rates between praziquantel and the combined treatment.

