### Sample size

The sample size is calculated using the statistical test for proportions based on the hypothesis that combination therapy using praziquantel plus an artemisinin-based combination is not inferior to praziquantel alone in treating schistosomiasis. Assuming a cure rate of 72% with praziquantel based on longitudinal studies from western Kenya [29], a cure rate of 62% (maximum difference of 10%) is considered clinically acceptable for non-inferiority of praziquantel plus an ACT combination therapy. With this non-inferiority margin, a power of 80%, and a one-sided alpha value of 0.025, a sample size of 102 children is needed in each treatment arm. To account for a 5% loss to follow-up, the total number of children to be enrolled and randomized is 540 (108 in each study arm).

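### The only statement of the non-inferiority rule is worded in reverse: read literally, it passes a combination whose lower confidence limit is at or below −10 points

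*Protocol article*

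**What the plan says.** The decision rule appears once, in the protocol article under Data management and analysis. The first sentence names the quantity: "The primary hypothesis for non-inferiority is assessed by considering the lower limit of the 95% CI for the risk difference". The next gives the criterion: "Non-inferiority is concluded if the lower bound of the 95%CI from the risk difference does not exceed the non-inferiority margin", with the margin given as −10. The same section defines the outcome as a cure rate and fixes the reference group: "children randomized to the PZQ alone study arm are considered the control group".

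Two other places bear on the rule without stating it:

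- The abstract (Methods) sets the margin at −10 "for the risk difference in cure rates between praziquantel and the combined treatment".
- The Sample size section takes 72% as the cure rate on praziquantel and says that "a cure rate of 62% (maximum difference of 10%) is considered clinically acceptable for non-inferiority", with a one-sided alpha of 0.025, 80% power and 102 children per arm.

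**The concern.** The margin is a negative number and the rule is an inequality on a signed lower limit. A number that does not exceed −10 is −10 or smaller. Since a higher cure rate is better, a lower limit at or below −10 means that a loss of 10 points or more has not been ruled out. That is exactly when non-inferiority should not be concluded. The sentence therefore names the failure region as the success region.

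The sentence governs the primary efficacy conclusion in all four comparisons with praziquantel alone. The article plans no interim analysis (Study and data monitoring), so the rule is applied once, at the end. Data analysts are not blinded (Randomization and blinding), so it is best not to leave the primary criterion to be reinterpreted once results are known.

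**Working it through.** **Inputs.** Control cure rate 72%, lowest acceptable cure rate 62%, one-sided alpha 0.025 and 102 children per arm, all from Sample size. Margin −10 points and a lower 95% limit, from Data management and analysis. The difference is taken as combination minus praziquantel alone. Intervals use the normal approximation with unpooled variance.

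**1. Which rule reproduces the plan's own alpha?** Take a combination exactly at the limit: true cure 62% against 72%, a true difference of −0.10.

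- SE = sqrt[(0.72 × 0.28 + 0.62 × 0.38)/102] = sqrt(0.4372/102) = 0.0655.
- P(lower limit > −0.10) = 1 − Φ[(−0.10 − (−0.10))/SE + 1.96] = 1 − Φ(1.96) = 2.5%. This is the stated one-sided alpha.
- P(lower limit ≤ −0.10) = 97.5%. This is the sentence as written.

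Only the rule with the lower limit above −10 agrees with the design.

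**2. Which observed differences pass under the literal wording?** With 72% cure in both arms:

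- Half-width = 1.96 × sqrt(2 × 0.72 × 0.28/102) = 1.96 × sqrt(0.4032/102) = 0.123, or 12.3 points.
- The lower limit is at or below −10 when the observed difference is at or below −10 + 12.3 = about +2 points.

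**3. Worked results, with 73 of 102 cured on praziquantel alone.**

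| Cured on combination | Difference (95% CI), points | Rule as written | Lower limit above −10 |
|---|---|---|---|
| 53/102 | −19.6 (−32.7 to −6.5) | non-inferior | not shown |
| 63/102 | −9.8 (−22.7 to 3.1) | non-inferior | not shown |
| 75/102 | +2.0 (−10.3 to 14.2) | non-inferior | not shown |
| 76/102 | +2.9 (−9.2 to 15.1) | not concluded | non-inferior |
| 83/102 | +9.8 (−1.8 to 21.4) | not concluded | non-inferior |

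The first combination is worse than praziquantel, with its whole interval below zero, and passes as written. The last has the higher observed cure rate and fails.

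**4. Probability of declaring non-inferiority, 102 per arm, control 72%.**

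| True cure on combination | Rule as written | Lower limit above −10 |
|---|---|---|
| 62% | 97.5% | 2.5% |
| 72% | 64.4% | 35.6% |
| 82% | 7.2% | 92.8% |

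As written, the chance of success falls as the combination gets better.

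**5. Dependence on the sample size.** The 102 per arm is used here only because the article states it. It does not follow from the stated inputs if both true cure rates are 72%: (1.96 + 0.842)² × 0.4032/0.10² gives about 317 per arm. That is a separate matter. The reversal is in the direction of the inequality and holds at any sample size. The +2-point threshold and the entries for 72% and 82% would change with the sample size, but the 97.5% and 2.5% at the margin would not.

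**The case against.** The strongest reply is that nobody would apply the sentence literally. In ordinary speech, not exceeding a margin means not going beyond it, so that the loss is no larger than 10 points. The Sample size section supports that reading: it hypothesises that the combinations are not inferior, accepts 62% against 72% as the limit, and uses a one-sided alpha of 0.025. With the abstract's margin of −10 and the use of the lower limit, only one working rule is coherent. This stands as evidence of intent, and the probabilities above therefore describe the sentence and do not forecast what the trial will report. It does not make the sentence correct: the reader has to override its words with another section to reach the intended rule. Nor is this a detail left to a statistical analysis plan, because the article states the rule and states it wrongly.

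A reader might infer three stronger points. The article does not support them.

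- **That a reversed test was planned.** The 62% limit and the alpha contradict this.
- **That the direction of subtraction is open**, because the abstract names praziquantel first. That phrase names two groups and sets no order. The Outcomes section compares each combination with praziquantel alone, the analysis section makes praziquantel alone the control and keeps the same order at week 12, and a negative margin with a lower limit makes sense only as combination minus control. The direction is implied, though no formula is written.
- **That Pearson's chi-square test, a test of equality, decides non-inferiority.** The article uses it to compare cure rates ("chi-square test for contingency tables (in a per-protocol analysis) and summarized as absolute risk differences") and separately bases the non-inferiority decision on the confidence interval.

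**Conclusion.** The point holds as an error of wording in the one sentence that states the primary decision rule. As written it contradicts the Sample size section and should be corrected. The intended rule, a lower limit above −10 percentage points, can be recovered with confidence from the Sample size section and the abstract, so the planned analysis itself is not in question.

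The size is conditional on a literal reading. With 102 evaluable children per arm and about 72% cure, every observed difference below about +2 points would be called non-inferior, and a combination truly at the unacceptable limit would pass about 97.5% of the time instead of 2.5%. These figures assume the normal approximation with unpooled variance and a difference taken as combination minus praziquantel alone.

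**What to change.** Replace the sentence under Data management and analysis with wording such as: *Risk difference = cure rate (PZQ plus ACT) minus cure rate (PZQ alone). Non-inferiority is concluded if the lower limit of its two-sided 95% CI lies above −10 percentage points.* Use the same direction and unit for the margin in the abstract, and carry the wording into the statistical analysis plan if there is one. Writing out the subtraction only makes explicit what the Outcomes and analysis sections already imply.

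The cost is one or two sentences. The endpoint, analysis population, interval, sample size and data collection are unchanged. The change is best recorded before the week 6 cure rates are compared between arms.

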### Outcomes

The primary efficacy outcomes are as follows:Cure rate at week 6 after starting study treatments, as assessed by microscopy. The cure rate on each PZQ plus ACT arm is compared with that on the PZQ alone arm.The number of participants with drug-related adverse events in the first 24 h after study treatment.

The secondary outcomes are as follows:Cumulative cure rate at week 12 after enrollment, as assessed by microscopy. The cure rate on each PZQ plus ACT arm is compared with that on the PZQ alone arm.Egg reduction rate at weeks 6 and 12 after starting treatment, as assessed by microscopy and intensity reduction rate, comparing each PZQ plus ACT with PZQ alone arm.The prevalence of re-infection at 12 after starting treatment, as assessed as the number of children who were cured at week 6 follow-up but positive for *S. mansoni* at the week 12 follow-up, compared each PZQ plus ACT arms to the PZQ alone arm.

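### The egg reduction rate is built on a mean taken over non-cured children only, which leaves out every zero count and gives an arm no direct credit for curing children

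*Protocol article*

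**What the plan says.** Under Outcomes, the ERR is a secondary outcome with a between-arm comparison: "Egg reduction rate at weeks 6 and 12 after starting treatment, as assessed by microscopy and intensity reduction rate, comparing each PZQ plus ACT with" praziquantel alone.

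The computation is in two consecutive sentences under Data management and analysis. The first introduces the abbreviation AM and its population: "Arithmetic mean (AM) egg counts are computed for all non-cured participants". The second uses it: "The egg reduction rate is computed as (1 − (AM EPG after treatment/AM EPG before treatment)) × 100". The formula names no population of its own, and the article defines no mean egg count over all treated children.

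The same section describes cured children as those "infected with *S. mansoni* at enrollment but not excreting eggs by week 6 after taking the study treatment". A child outside the non-cured group therefore has a follow-up count of zero.

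**The concern.** An ERR is meant to describe how far egg output falls in a treated group. If the mean is restricted to children still excreting eggs, the children whose output fell by 100% are left out.

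There are two consequences. First, membership of the analysed group depends on what happened after randomisation, so the groups compared are no longer the randomised arms. An arm that cures more children is represented by a smaller and possibly quite different set of failures. Second, the cure rate no longer enters the ERR, so the ERR can miss or misrepresent the benefit that the combinations are hoped to add. At stake is a named comparative efficacy outcome at two time points.

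**Working it through.** The article states no ERR value, no baseline mean EPG and no residual mean EPG, so there is no figure to reproduce. The check applies the stated rule and the all-children version to the same inputs.

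**Inputs from the article (Sample size).** Control cure rate: "Assuming a cure rate of 72% with praziquantel based on longitudinal studies from western Kenya". Arm size: "a sample size of 102 children is needed in each treatment arm".

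**Assumed inputs.** Baseline mean 200 EPG, the same in non-cured and in all children; follow-up mean 60 EPG among non-cured praziquantel children; 90% cured in a combination arm, with its non-cured mean varied.

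**Step 1: who is left out.** 0.28 × 102 = 28.6, so about 29 children enter the mean and about 73 do not. This is exact where cure is judged at the visit being analysed; the article does not say which visit defines non-cured for the week 12 ERR.

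**Step 2: direction.** Let c be the cure rate, M the follow-up mean among the non-cured, and B, B_N and B_C the baseline means among all, non-cured and cured children. Cured children contribute 0 at follow-up.

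- All children: ERR = 1 − (1 − c)M/B.
- Rule, only the follow-up mean restricted: ERR = 1 − M/B. This is lower whenever c > 0 and M > 0.
- Rule, both means restricted: ERR = 1 − M/B_N. This is lower whenever B > (1 − c)B_N. Since B = (1 − c)B_N + cB_C, and B_C > 0 because every enrolled child had eggs in stool, it is always lower.

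The understatement therefore needs no assumption about egg counts. The rule drops the factor (1 − c), which is where an arm gets credit for curing children.

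**Step 3: size in one arm.** With c = 0.72, B = B_N = 200 and M = 60:

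- Rule: 1 − 60/200 = 70.0%.
- All children: 1 − 0.28 × 60/200 = 1 − 16.8/200 = 91.6%.

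**Step 4: comparison with a 90%-cure arm.** Differences are combination minus praziquantel, in percentage points.

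| Non-cured mean, combination | ERR, rule | Difference, rule | ERR, all children | Difference, all children |
|---|---|---|---|---|
| 40 | 80.0% | +10.0 | 98.0% | +6.4 |
| 56 | 72.0% | +2.0 | 97.2% | +5.6 |
| 60 | 70.0% | 0.0 | 97.0% | +5.4 |
| 80 | 60.0% | −10.0 | 96.0% | +4.4 |

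Under the rule the combination ranks lower once its non-cured mean exceeds 60. Over all children it ranks lower only when 0.10 × M > 16.8, that is, M > 168. Between 60 and 168 the two versions rank the arms in opposite order; below 60 they agree on order but not on size.

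**Step 5: range under simulated counts.** Assumptions: gamma baseline EPG (shape 0.6, mean 250 before children with a zero baseline count were dropped), beta-distributed residual egg output with varying mean and spread, and the average of two readings × 24 at each time.

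| Scenario | Cure rate | ERR, all children | ERR, non-cured in both means | ERR, non-cured after / all before |
|---|---|---|---|---|
| 1 | 73.4% | 90.0% | 71.3% | 62.2% |
| 2 | 85.6% | 95.1% | 74.3% | 65.6% |
| 3 | 91.6% | 95.0% | 51.5% | 40.8% |
| 4 | 83.7% | 90.0% | 49.4% | 38.5% |
| 5 | 94.9% | 97.1% | 52.5% | 42.4% |
| 6 | 76.3% | 95.1% | 85.6% | 79.1% |

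With both means restricted, the understatement runs from about 9.5 points (scenario 6) to 44.6 points (scenario 5). It is larger when the baseline mean covers everyone. Against scenario 1, scenario 2 is about 5.1 points better over all children but about 3.1 under the rule (difference shrinks). Scenario 3 is about 5.1 points better over all children but about 19.8 worse under the rule (order reverses). Scenario 6 is about 5.1 points better over all children and about 14.3 under the rule (difference widens).

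**The case against.** The strongest defence is that the AM sentence is a separate description of residual intensity among treatment failures, and that the formula, which names no population, is meant for all children. That reading is possible. But the AM sentence stands directly before the formula and is the only place that says whose counts are averaged, so an analyst following the text would use it. Even on the kinder reading, the ERR population is fixed badly and needs one sentence to settle it.

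A second defence is that every EPG value above is assumed. This stands for the size and for the ranking of arms, but not for the direction of error within an arm (step 2).

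A third is that the ERR is secondary. That is correct: the week 6 cure rate, its risk difference, the non-inferiority decision and the safety analysis do not use it.

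A reader might infer more than the article supports in two ways. One is that a better arm will look worse. Step 4 and scenarios 2 and 6 show that it need not; the outcome depends on residual counts that the article does not give. The other is that the ERR comparison also suffers from uncorrected pairwise testing, because the section says: "The least significant difference will be used to assess post hoc pair-wise comparisons between the group means". That sentence follows the one on analysis of variance for changes in continuous variables. The ERR as defined is one number per arm and cannot enter such a test directly, and Outcomes plans only the four contrasts with praziquantel alone. The text does not tie the least significant difference to the ERR.

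**Conclusion.** The concern holds for the ERR population. As written, the rule conditions on a post-randomisation outcome, drops about 73 of 102 children in the praziquantel arm at the plan's own cure rate, and understates the ERR in any arm that cures some children but not all. In the one-arm illustration the gap is 21.6 points (91.6% against 70.0%), resting on the assumed 200 and 60 EPG. Under the simulated distributions with both means restricted it runs from about 9.5 to 44.6 points. The effect on the comparison between arms cannot be predicted from the article: a difference can shrink, vanish or reverse, and reversal is not inevitable.

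This should be fixed. It is not critical, because the outcome is secondary and the primary analysis is untouched.

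**What to change.** Replace the AM sentence and complete the formula along these lines:

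*For the ERR at each follow-up visit, arithmetic mean EPG before and after treatment is computed over the same children: all children in the analysis population who were infected at baseline and have a stool result at that visit, with cured children counted as 0 EPG. ERR = (1 − AM after / AM before) × 100. Each praziquantel-plus-ACT arm is compared with praziquantel alone, with a confidence interval for the comparison. Mean EPG among non-cured children is reported as description only.*

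A bootstrap is one convenient way to obtain the interval; the choice is open.

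Add a sentence on missing results that agrees with the imputation rule in the same section. Where a missing result is imputed as a success, the child enters at 0 EPG; where it is imputed as a failure, the child enters at the baseline EPG, which matches that rule's assumption of unchanged intensity.

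The cost is a few sentences in the protocol or analysis plan and a few lines of code. No new data are needed, because zero counts are already produced by the planned stool examinations. Because the data analysts are not blinded, the change should be dated and, if possible, made before the ERR is tabulated by arm.
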